### Study objectives

The primary objective of the study is to evaluate the effect of continuous antepartum eCTG monitoring on severe perinatal morbidity and mortality, by comparing with conventional intermittent CTG monitoring. The objectives are investigated in preterm fetuses (GA 23–32 weeks) whose mothers are admitted to the OHC. The primary study outcome is a composite outcome consisting of (1) Perinatal mortality, defined by the WHO as: deaths that occur after a gestational age of ≥22 weeks or, if unknown >500 gram, until 28 days after birth^20^ and (2) Major neonatal morbidity assessed at the time point when the neonate is discharged from the hospital.^21^ Major neonatal morbidity is defined as either: intraventricular haemorrhage (IVH) grade three or more,^22 23^ periventricular leukomalacia (PVL) grade two or more,^24 25^ moderate or severe bronchopulmonary dysplasia (BPD),^26^,^28^ necrotising enterocolitis (NEC) grade two or more,^29 30^ or retinopathy of prematurity (ROP) necessitating laser therapy.^31^ Secondary study objectives are the effect of continuous antepartum eCTG compared with conventional intermittent CTG monitoring on maternal mortality, neonatal morbidity, satisfaction for both patient and caregiver, duration of pregnancy, the need to switch between monitoring methods (either from eCTG to CTG or vice versa), timing and number of obstetric interventions, duration of admission at the OHC and admission and duration of admission at the neonatal intensive care unit. Demographics will be obtained from the electronic patient file. The secondary outcomes are defined as follows: maternal mortality as defined by the WHO^32^: any death from any cause related to or aggravated by pregnancy or its management (excluding accidental or incidental causes) during pregnancy and childbirth or within 42 days of termination of pregnancy, irrespective of the duration and the site of the pregnancy. Neonatal morbidity, excluding major neonatal morbidity described as primary outcome, is defined as: Any health condition attributed to and/or aggravated by birth, assessed at the time point when the neonate is discharged from the hospital^21^ or—if discharged within 4 weeks after birth—at 4 weeks after birth, that has negative outcomes to the neonatal well-being (ie, IVH grade 1–2, PVL grade 1, mild BPD, NEC grade 1, ROP (any grade)) not necessitating laser therapy, hypoxic ischaemic encephalopathy, neonatal seizures, neonatal sepsis (culture proven), need for intubation on the delivery room, mechanical ventilation within the first 72 hours after birth, antibiotics within the first 72 hours after birth, spontaneous intestinal perforation necessitating surgery, surfactant treatment, Apgar score <7 after 5 min, severe metabolic acidosis (pH <7.05 and base deficit ≥12 mmol/L). This definition of severe metabolic acidosis is set at pH <7.10 and base excess ≥12 mmol/L in cases with only an umbilical vein sample (one available blood gas sample or the pH difference between two samples below 0.03^33^). Next to the study objectives described above, the data that is gathered in this study will be used to develop and verify mathematical models that aim at the prediction of time to (premature) birth and at automated detection of foetal movements.

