#### Data collection

All required demographic and medical information will be obtained from the EPR at the Máxima MC or the referring hospital, when the patient has been transferred to or from this hospital before or after their admission to the OHC. This includes maternal and perinatal information. For the mother: age, ethnicity, BMI, obstetric history, general medical history, medication use, intoxications, information about the course of pregnancy, complications during pregnancy, delivery and (until 6 weeks) postpartum, For the fetus/neonate: ultrasound results such as foetal biometry, structural abnormalities or Doppler measurements, gestational age at delivery, gender, birth weight, admission to neonatal ward and the reason for admission, Apgar scores, pH and base excess in umbilical artery and vein, mortality, morbidity, general information on neonatal health in the first 4 weeks postpartum. Research Manager (ISO 27001 certified) is used to store patient data.

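### The venous-sample rule for severe metabolic acidosis is written with base excess where the rule beside it uses base deficit, so its sign is reversed; this affects one component of a secondary outcome

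*Protocol article*

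**What the plan says.** Under Study objectives, the Protocol article lists the conditions that make up secondary neonatal morbidity. This outcome is kept apart from the primary one: "Neonatal morbidity, excluding major neonatal morbidity described as primary outcome". One item on the list is "severe metabolic acidosis (pH <7.05 and base deficit ≥12 mmol/L" (the general rule below).

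The next sentence changes that definition for some neonates. For them it is set at "pH <7.10 and base excess ≥12 mmol/L in cases with only an umbilical vein sample" (the venous rule below). The same sentence says when this applies: "one available blood gas sample or the pH difference between two samples below 0.03".

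Under Data collection, the cord-gas variables taken from the patient record are "pH and base excess in umbilical artery and vein". Base deficit is not listed, and nothing says that base excess is stored as an absolute value or with its sign reversed.

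**The concern.** Two adjacent sentences define the same condition, but one sets a lower bound on base deficit and the other sets the same lower bound on base excess. On the usual signed scale these are opposite requirements. A low pH with a base excess of +12 mmol/L or more is a base surplus, not a metabolic acidosis.

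The slip would be easy to carry into a program because the venous rule uses the name of the variable that is actually recorded. An analyst could apply it to the data column as printed. The venous rule also replaces the general rule in its subset and does not add to it. A neonate with a single sample who clearly met the general rule would therefore be scored as not acidotic. What is at stake is an undercount of severe metabolic acidosis in neonates with one sample or two near-identical samples.

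**Working it through.** No figure in the plan needs to be reproduced here, so the check is one of logic.

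**Inputs, all from the Protocol article**
- General rule (Study objectives): pH below 7.05 and base deficit (BD) ≥12 mmol/L.
- Venous rule as printed (Study objectives): pH below 7.10 and base excess (BE) ≥12 mmol/L.
- Recorded variable (Data collection): base excess.

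**Step 1. Put both rules on the recorded scale.** BD = −BE.
- General rule: BD ≥ 12 means BE ≤ −12.
- Venous rule as printed: BE ≥ +12, which means BD ≤ −12.

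No value of BE is both ≤ −12 and ≥ +12, so no sample can meet both base conditions.

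**Step 2. Apply the rules to test values.** The values are chosen for illustration and are not trial data. The last column is the venous rule with its sign made consistent with the general rule.

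| pH | BE | BD | General rule (pH <7.05, BD ≥12) | Venous rule as printed (pH <7.10, BE ≥12) | Venous rule, consistent sign (pH <7.10, BE ≤ −12) |
|---|---|---|---|---|---|
| 7.00 | −16 | 16 | yes | no | yes |
| 7.04 | −12 | 12 | yes | no | yes |
| 7.08 | −14 | 14 | no | no | yes |
| 7.09 | −12 | 12 | no | no | yes |
| 7.09 | −11.9 | 11.9 | no | no | no |
| 7.09 | 0 | 0 | no | no | no |
| 7.09 | +11.9 | −11.9 | no | no | no |
| 7.09 | +12 | −12 | no | yes | no |

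The consistent rule accepts four samples and the printed rule accepts none of them (0 of 4). The only sample that the printed rule accepts has a base surplus. The first two rows meet even the stricter pH limit of the general rule. They would still be scored negative if they came from a neonate in the venous subset, because there the venous rule takes the general rule's place.

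**Step 3. Establish the reach.** The venous rule governs neonates with one sample and those with two samples whose pH differs by less than 0.03. The article gives no count or share for this subset. If a share *s* of all true acidosis cases falls in it, literal coding finds about 1 − *s* of the cases. Since *s* is not given, the loss cannot be computed.

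**The case against.** The strongest reply is that the intent is plain. The second sentence presents itself as an adaptation of the first: it raises the pH limit and keeps the threshold, the direction of the inequality and the unit. Under the name of severe metabolic acidosis with a pH below 7.10, hardly any reader would take it to require a base surplus. An analyst who saw almost no positive cases in the subset would probably notice. The article also refers to a full protocol (version 9) that is not shown, and the operational definition there may be correct. All of this stands. It makes the point a probable wording slip and makes the harm conditional on literal coding. It does not make the printed threshold right.

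A reader might infer more than the documents support, in three ways.

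- **Bias between the groups.** By the Sample size section, the conventional CTG comparator is 1400 + 37 + 37 = 1474 women, of whom 1400/1474 = 95% are historical, while the eCTG group is wholly prospective. If the venous rule applied more often in one period than in the other, the undercount would differ between groups, and a propensity score would not repair a misclassified outcome. But the article gives no frequency of single or near-identical samples in either cohort and does not suggest that they differ. A figure would also need acidosis to be equally common in both sample types. Any ratio quoted would be an assumption and not a result.
- **Damage to the main result.** Acidosis is not part of the primary composite, and no acidosis rate enters the sample size. If secondary neonatal morbidity is scored as any listed condition, a missed acidosis changes a neonate's status only when no other item is present. The list includes surfactant, delivery-room intubation, and ventilation or antibiotics in the first 72 hours, in pregnancies enrolled at 23 to 32 weeks.
- **No acidotic neonate found at all.** That is too broad. Neonates outside the venous subset are classified by the general rule, which is correctly signed. Inside it, an extreme respiratory acidosis with a positive base excess could formally pass the printed rule.

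**Conclusion.** The point holds as a sign error in a stated outcome threshold. The two rules under Study objectives contradict each other, and the one in error uses the name of the recorded variable. If it is coded literally on signed base excess, essentially all metabolically acidotic neonates in the venous subset are missed. This rests on two assumptions: base excess is stored with its usual sign, which the article neither states nor denies, and the database derivation follows the printed text.

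The consequence is confined to that subset of one component of the secondary neonatal morbidity outcome. It matters most if acidosis is reported as a separate item. Its size, and any difference between groups, cannot be derived from the documents. It is a small correction that should still be made, because the error would otherwise pass silently into the data.

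**What to change.** Write both rules with one term and one sign: base deficit ≥12 mmol/L, that is base excess ≤ −12 mmol/L, keeping the pH limits as they stand. Because base excess is the recorded variable, giving the base-excess form for both rules removes the ambiguity.

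Then check that the derivation in the study database uses that sign, and that base excess is stored with the same sign in the historical and prospective records. It would also help to record which rule classified each neonate, so that the size of the venous subset can be reported by cohort.

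The cost is a one-line text correction and a short check of the derivation. No new data, change to the sample size or change to the analysis is needed.

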
### Population

To be eligible to participate in this study, women must be 18 years or older, with a singleton pregnancy between 23+0 and 32+0 weeks of gestation that requires hospitalisation to the OHC for foetal monitoring and parents wishing for foetal monitoring (table 1). Exclusion criteria are multiple pregnancy, contraindications to abdominal patch placement (eg, abdominal skin disease), women connected to external or implanted electrical stimulators, foetal or maternal cardiac arrhythmias, insufficient knowledge of Dutch or English language, women admitted with a clinical diagnosis of sepsis with hypotension (ie, septic shock), or when the treatment plan (with intervention planned within 24 hours) is already made before inclusion has been completed (table 1). Included participants can withdraw from study participation at any time without giving reason and without any consequences.

**Table 1 T1:** Inclusion and exclusion criteria

Inclusion criteria	Exclusion criteria
Maternal age ≥18 years	External or implanted electrical stimulator
Singleton pregnancy	Multiple pregnancy
GA 23+0–32+0 weeks	Foetal or maternal cardiac disease
Requiring hospitalisation to the OHC for foetal surveillance	Contraindication to abdominal patch placement (eg, abdominal skin disease)
Parents wishing for foetal monitoring	Intervention planned <24 hours before inclusion is completed
	Women admitted with a clinical diagnosis of sepsis with hypotension (ie, septic shock).
	Insufficient knowledge of Dutch or English language

GA, gestational age; OHC, obstetric high care.

### Patient and public involvement

Care4Neo, Neonatal Patient and Parent Advocacy Organization, Rotterdam, The Netherlands, reviewed the study protocol from a patient and parent perspective in the funding stage. They also reviewed and contributed to the patient information leaflet.

### Study design

The CIRSS was chosen to balance methodological rigour with feasibility and ethical considerations in a high-risk obstetric population. This design feature has recently been described and compared with other study designs^34^, highlighting its ability to combine real-world applicability with robust statistical correction for potential biases. The use of historical controls and random sampling within a prospective cohort allows for efficient implementation and broader inclusion, while maintaining internal validity through causal inference techniques such as inverse probability weighting with a per-protocol analysis. This CIRSS design has two components: a prospective data collection and a retrospective data collection (figure 1).

**Figure 1 F1:**
[figure not shown]
Cohort intervention random sampling study (CIRSS) design. Informed consent (IC) is asked after the patient is sampled or not. CTG, cardiotocography; eCTG, electrophysiological cardiotocography; MMC, Máxima Medical Centre; NFMS, Nemo Foetal Monitoring System; OHC, obstetric high care, EPD, electronic patient documentation.

#### Prospective recruitment

Potential participants will be informed about the study by their obstetric healthcare professional when admitted to the hospital. First, the healthcare professionals will verify the inclusion and exclusion criteria (table 1), after which the women are added to the study using an encryption key. These women are part of the cohort study and receive standard care consisting of conventional intermittent CTG monitoring. A part of these women will be randomly sampled. This random sampling is conducted by the research team using a secure algorithm embedded in Research Manager (ISO 27001 certified). They will be offered the new treatment: continuous eCTG monitoring using the NFMS (figure 2). The women will either be part of the cohort study, thus receiving standard care consisting of conventional intermittent CTG monitoring, or they will be sampled for continuous eCTG monitoring using the NFMS. Appropriate explanation and written study information will be provided hereafter by the healthcare professional, and they will ask the researchers for further counselling. Non-sampled women will only receive information regarding the collection of their data in the cohort study. Sampled women will be informed about receiving continuous eCTG monitoring. A researcher will complete the informed consent (IC) procedure, including collecting written consent (for an example of the participant consent form, see online supplemental file 1). When the women do not wish to participate in the study, they will be excluded, their encrypted information will be obliterated and the exclusion will be anonymously documented. Once women are included, they are given the appropriate monitoring method. Five NFMS devices are available at the OHC of Máxima MC. When no NFMS device is available within 24 hours after sampling and inclusion, the sampled women will receive standard treatment within the study. For continuous monitoring, trained nursing staff will oversee device placement and signal quality checks during routine care. CTG traces are continuously displayed on a central monitoring system, where deviations from normal patterns trigger automated alarms to alert clinical staff. In addition, CTG traces are systematically assessed by physicians at least four times per 24 hours at predefined intervals, partly retrospectively, and more frequently if clinically indicated. These assessments follow a standard operating procedure (SOP) to ensure consistency and clinical relevance. If the eCTG recording does not provide sufficient signal quality for reliable monitoring, we will report this and, if needed, can be switched to standard CTG monitoring. This decision will be made on the clinical judgement of the attending gynaecologist. No literature was available on an acceptable signal loss threshold. The International Federation of Gynaecology and Obstetrics Guidelines advises switching monitoring methods in intrapartum monitoring when a signal loss threshold of 20% is reached.^35^ Based on this, a standardised protocol for switching to conventional CTG will be implemented when signal loss exceeds 20%, or when clinical judgement deems the eCTG trace insufficient for reliable interpretation. This protocol will be documented and monitored throughout the study. Women who decline to be part of the cohort will receive standard care: conventional CTG monitoring without data collection for research. All prospectively included women will receive a digital invitation to two digital surveys. Women are asked to fill in the first survey about their experience with the received monitoring method—EQ5D5L questionnaire^36^—on the first day after admission, and the second survey about their experience—D-QUEST^37^—on the last day of admission. Although the patient satisfaction surveys are administered at admission and discharge, all participants are followed up until (at least) 4 weeks postpartum. During this period, patients have the opportunity to share additional reflections or concerns with their care team, which may provide further qualitative insights into their experience with the monitoring method.

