#### Retrospective recruitment

In order to strengthen the comparison of the two groups (continuous eCTG monitoring and conventional intermittent CTG monitoring), additional data from women who received standard treatment (conventional intermittent CTG monitoring) in Máxima MC Veldhoven, the Netherlands in 2014–2019 will be collected retrospectively. Data will be derived from electronic patient records (EPRs).

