### Statistical analysis

For the primary and secondary outcomes, based on the demographics, characteristics of the women and their baseline outcomes, a propensity score will be created. This will be used to correct for possible selection bias that may occur due to (1) the group of women who are offered eCTG but receive CTG (either by choice or circumstances) or (2) the retrospective and prospective nature of the study. Thus, a per-protocol analysis with propensity score adjustment will be considered. The propensity score models will include maternal characteristics (eg, age, BMI, parity, ethnicity), foetal indicators (eg, gestational age, foetal growth restriction, Doppler abnormalities) and care-related variables (eg, indication for admission, medication use, duration of hospitalisation). These covariates were selected based on clinical relevance and availability across both cohorts. For categorical outcomes, a logistic regression analysis will be applied to estimate the treatment effect corrected for the propensity score. For numerical outcome values, a general linear model will be applied with an appropriate probability distribution link function and the sandwich estimator to estimate a treatment effect corrected for the propensity score. For time-to-event outcome, a Cox proportional hazards model will be used with a sandwich estimator to estimate a treatment effect corrected for the propensity score. For the data gathered from the questionnaires, standard statistical tests will be used (χ^2^, t-test, Mann-Whitney tests) to determine a difference between the two treatment groups. A propensity score approach will be applied as well if large imbalances between characteristics are present between CTG and eCTG participants. Several sensitivity analyses are being anticipated. The combined endpoint will be analysed as separate end-points. Several subgroup analyses are investigated (eg, obesity). A p value of <0.05 is considered statistically significant unless otherwise specified. When possible, 95% CIs will be calculated for the reported measures of effect. Missing data will be evaluated and reported. Limited missing data is expected, and if missingness is less than 5%, list-wise deletion will be used. Otherwise, multiple imputation (eg, predictive mean matching) will be used. The imputation will be repeated at least 10 times and Rubin’s rule will be used to combine estimates and standard errors from the imputed data.

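### No common time zero: eCTG recipients must still be undelivered with a live fetus when the device is fitted, and historical controls face no such condition

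*Protocol article*

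**What the plan says.** Under Prospective recruitment, the protocol article puts the steps in this order: eligibility check, random sampling, counselling and written consent, then the allocated monitoring. On capacity it says "Five NFMS devices are available at the OHC of Máxima MC", and on shortage "When no NFMS device is available within 24 hours after sampling and inclusion, the sampled women will receive standard treatment within the study". The 24 hours run from sampling and inclusion, not from admission.

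Under Statistical analysis it says "Thus, a per-protocol analysis with propensity score adjustment will be considered". One of the two sources of selection bias that the propensity score is meant to handle is "the group of women who are offered eCTG but receive CTG (either by choice or circumstances". The listed covariates are mostly baseline features, but they include duration of hospitalisation. A Cox model is planned for time-to-event outcomes.

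Under Sample size, the expected groups by monitoring received are 335 women on eCTG, 37 sampled women who decline it, 37 non-sampled women and 1,400 historical women.

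Under Retrospective recruitment, the historical data are "additional data from women who received standard treatment (conventional intermittent CTG monitoring" in 2014–2019. No index date is given.

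Under Population, the text excludes women "when the treatment plan (with intervention planned within 24 hours) is already made before inclusion has been completed", whereas Table 1 has "Intervention planned <24 hours before inclusion is completed". The text excludes fetal or maternal cardiac arrhythmias, whereas Table 1 has "Foetal or maternal cardiac disease".

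**The concern.** Membership of the eCTG group is settled only when the device is fitted, after sampling, consent and possibly a wait. A woman who delivers or loses the fetus before then cannot become an eCTG recipient. A historical woman with the same course remains a control, because nothing in her care corresponds to sampling, consent to a new monitor, or fitting.

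Fetal death and the major morbidity of the preterm neonate are the primary outcome itself, so this filter acts on the outcome. For the binary composite the result is selection bias. For the Cox outcomes it is immortal time.

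A propensity score balances covariates measured at a common starting point. Remaining undelivered until fitting is not such a covariate. Duration of hospitalisation tracks it, but is known only after time zero, so adjusting for it is not a valid repair. At stake is an apparent benefit of eCTG that could arise with no true effect.

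**Working it through.** **1. Which groups are compared.** CTG recipients: 1,400 + 37 + 37 = 1,474. Historical share: 1,400/1,474 = 95%. eCTG recipients: 335.

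**2. The plan's own figure.** Inputs from Sample size: 17% control risk, an effect of 6% read as 6 percentage points (17% v 11%), 80% power, 5% type I error (two-sided assumed).
- Pooled risk: (1,474 × 0.17 + 335 × 0.11)/1,809 = 0.1589
- Null SE: √[0.1589 × 0.8411 × (1/1,474 + 1/335)] = 0.02213
- Alternative SE: √[0.17 × 0.83/1,474 + 0.11 × 0.89/335] = 0.01970
- Power: Φ[(0.06 − 1.96 × 0.02213)/0.01970] = 80.1%

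The stated power is reproduced with groups defined by monitoring received, so that is the comparison the study was sized for.

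**3. Size of the filter under no true effect.** The documents do not give the share f of women otherwise destined for eCTG who deliver or lose the fetus before fitting, nor their composite risk q. Both are assumptions. Overall risk is held at 17%, these women are counted as CTG, and no covariate adjustment is made.
- Women moved: m = 335f
- eCTG risk: (0.17 − fq)/(1 − f)
- CTG risk: (1,474 × 0.17 + mq)/(1,474 + m)

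Worked case, f = 5%, q = 50%: m = 16.75; eCTG risk (0.17 − 0.025)/0.95 = 15.26%; CTG risk (250.58 + 8.375)/1,490.75 = 17.37%; difference 2.11 points, or 35% of the planned 6.

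| f | q | eCTG | CTG | Spurious benefit (points) | Two-sided type I error |
|---|---|---|---|---|---|
| 1% | 25% | 16.92% | 17.02% | 0.10 | 5.0% |
| 2% | 50% | 16.33% | 17.15% | 0.82 | 6.2% |
| 5% | 25% | 16.58% | 17.09% | 0.51 | 5.4% |
| 5% | 35% | 16.05% | 17.20% | 1.15 | 7.4% |
| 5% | 50% | 15.26% | 17.37% | 2.11 | 14% |
| 10% | 50% | 13.33% | 17.73% | 4.40 | 46% |

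If q = 17% the bias is zero. If q exceeds 17% it favours eCTG.

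**4. If women with pre-fitting events were dropped instead.** The difference is then 0.17 minus the eCTG risk: 0.08 points for f = 1%, q = 25%, and 3.67 points for f = 10%, q = 50%. It is smaller, but in the same direction.

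**5. Power after alignment.** Remove a share f from both groups at a common landmark, do not replace them, and keep 17% v 11%. With f = 5% (1,400 v 318) power is 77.9%; with f = 10% (1,327 v 302) it is 75.4%. Grouping by sampling (372 v 1,437), with the effect diluted to 0.9 × 6 = 5.4 points, gives 73.8%.

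**The case against.** The strongest reply is that the bias may be very small. The 24-hour rule concerns device shortage, which depends on ward load rather than on the woman's own course, so sending such women to CTG is not in itself driven by outcome. Twenty-four hours is a ceiling: the article says women receive the appropriate method once included, so fitting may usually be prompt. Women with an intervention already planned within 24 hours are excluded, which removes some foreseeable early deliveries. The propensity model includes gestational age, indication for admission and Doppler findings, all plausible predictors of imminent delivery. And an article condenses the full protocol.

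Most of this stands as a limit on size. It does not remove the mechanism: unplanned delivery and fetal death before fitting are not covered by the exclusion, the time taken by consent adds to any device wait, and baseline covariates do not account for having remained undelivered.

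A reader might also infer that historical women are counted from admission, or that women who deliver before fitting are expressly counted as CTG. The article says neither. The second is a natural reading of the wording on circumstances together with a per-protocol analysis, but it remains an inference, and dropping those women would still favour eCTG. Nor does the article say that historical women are exempt from the planned-intervention exclusion; it is silent on this.

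**Conclusion.** The point holds in this form: no common time zero is fixed, and grouping by monitoring received after sampling, consent and a possible device wait, against historical controls with no such step, filters early events out of eCTG only. This goes beyond missing detail, because the stated remedy does not address it.

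The direction favours eCTG provided that women with early events have above-average risk. The size is unknown. The range of about 0.1 to 4.4 points rests on assumed shares of 1–10% and risks of 25–50%, with no adjustment and no allowance for the planned-intervention exclusion. The low end is plausible if fitting is prompt. A reader might infer from the upper rows of the table that a false positive is likely; the documents do not support that, since nothing in them gives the share or the risk. The stated 80% power is not in error.

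The contradictions between the Population text and Table 1 are real, but they are a separate matter and add no weight to the time-zero argument.

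**What to change.** 1. Define one index time that exists in the records of every group, and one landmark after it long enough to cover sampling, consent and the full device window. Twenty-four hours from admission is too short, because the device window starts only at sampling and inclusion.
2. Include in the primary comparison only women undelivered with a live fetus at the landmark, and classify monitoring by status at the landmark. Apply the same rule to eCTG, concurrent CTG and historical women, using date-times from the electronic patient record. Start the Cox outcomes at the landmark.
3. Leave duration of hospitalisation out of the propensity model, or restrict it to time accrued before the index time.
4. Add a sensitivity analysis that keeps sampled women in the sampled group whatever monitoring they received. It removes the fitting condition but not the consent step, so it complements the landmark and does not replace it.
5. Separately, reconcile the Population text with Table 1 (cardiac arrhythmias v cardiac disease; the two 24-hour wordings) and apply the reconciled list to the historical records.

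Cost: protocol and analysis-plan wording, extraction of date-times, and review of some further historical records. Women removed by the landmark also include prospective women. If they are not replaced, power falls from 80.1% to about 77.9% (5% removed) or 75.4% (10% removed). The result will apply only to women still pregnant at the landmark. Sampling only when a device is free would shorten the wait, but it changes the sampling procedure and is a trade-off for the sponsor. All of this should be settled before historical records are selected and outcomes are analysed.
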